### Secondary outcomes

- Anxiety, depression, and distress (validated scales).

- Health-related quality of life (EQ-5D-5L).
- Proportion of participants scoring above/below the FCRI-SF cut-off ( $\geq 22$ ).
- Adherence and engagement metrics (number of modules completed, communication with therapist).

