## AIM

The primary aim of this randomized controlled trial (RCT) is to test if a therapist-guided version of iConquerFear (TG-iConquerFear) can reduce FCR and improve QoL for CRC survivors more than augmented treatment as usual (augmented TAU).

Secondary objectives are to i) outline the prevalence of FCR in a population based CRC cohort up to 5 years post-diagnosis using a validated FCR measure with a clinical cut-off. This comprehensive screening will be used as recruitment for the RCT; ii) Investigate whether being diagnosed as a consequence of the Danish Nation-wide Colorectal Cancer Screening Program increases FCR compared to being diagnosed as a consequence of physical symptoms; and iii) investigate whether FCR is associated with anxiety, depression, bodily distress syndrome and health anxiety in CRC survivors as well as investigate whether uncertainty in illness, negative beliefs about worry and perceived risk of cancer recurrence act as moderators or mediators of FCR.

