## Procedure

### Part 1, survey

The CRC survivors will be invited by mail to their secure, personal electronic box (E-boks) to electronically fill out the 63-item screening questionnaire comprising: The FCRI-short form (FCRI-SF) assessing FCR severity, bodily distress symptoms (BDS checklist), health anxiety (Whiteley-8), anxiety (SCL4-anx), depression (SCL6-dep), and two items assessing global overall health and global quality of life (Visual Analogue Scale (VAS) 0-100). Two items asks for time since last cancer surveillance visit at the hospital and time until next visit. Participants are asked to answer yes or no regarding received chemotherapy or radiation. One item asks for consent to answers being used for research in anonymous form. Questionnaires and supplemental questions are listed in appendix 6 (Spørgeskemaer).

Completed questionnaires will be exported directly into the RedCap database for clinical research. Those with no access to Internet will be invited by paper and the data will be manually entered in RedCap. In case of no response, a reminder will be send after 2 weeks. All participants will be informed of their current level of FCR based on their answers.

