### Secondary outcome measures

Change from baseline (Tb) to post-intervention (T0, T1, T2, T3) in the following outcomes

- *Bodily Distress Symptom/somatization, Anxiety and depression* evaluated by relevant Symptom Checklist-90-R (SCL) subscales [52], validated in Danish by Olsen et al [53].
- *Health Anxiety* measured by the validated [54] Whiteley-8 index [55].
- *Global quality of life and global health* measured by a VAS 0-100

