### Secondary hypotheses

- TG-iConquerFear will reduce anxiety, depression, and distress, and improve quality of life.
- TG-iConquerFear will not affect the prevalence of physical symptoms.
- Some participants will demonstrate particularly high engagement and adherence with the online format, which may be associated with distinct demographic or psychosocial characteristics.

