### 5.3 Secondary analyses

- Continuous secondary outcomes analyzed using paired *t*-tests and between-group comparisons of change scores.
- Longitudinal analyses across baseline, 1/2, 3, and 6 months using **linear mixed-effects models**, with fixed effects for group, time, and interaction, and random intercepts for subjects.
- Proportions above/below clinical cut-offs analyzed using  **$\chi^2$  tests**.
- Reliable and clinically significant change indices calculated.

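### The SAP's secondary outcomes conflict with the protocol: quality of life moves to EQ-5D-5L, the VAS items and health anxiety are not named, and the mixed model leaves out one year

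*Combined protocol and SAP*

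**What the plan says.** The protocol's Aim asks whether the intervention "can reduce FCR and improve QoL for CRC survivors more than augmented treatment as usual". Under Part 1, survey, the screening questionnaire includes "two items assessing global overall health and global quality of life (Visual Analogue Scale (VAS) 0-100". Under Secondary outcome measures, the protocol sets out "Change from baseline (Tb) to post-intervention (T0, T1, T2, T3) in the following outcomes", then lists bodily distress, anxiety and depression on SCL subscales, health anxiety "measured by the validated [54] Whiteley-8 index [55", and the two global items "measured by a VAS 0-100". The protocol's Fig. 2 timeline has rows for QoL and Whiteley-8 at population screening, follow-up and close-out. The Primary outcome measure section also plans a long-term evaluation at one year (T3).

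In the SAP, section 4 gives as the quality-of-life outcome "Health-related quality of life (EQ-5D-5L". Anxiety, depression and distress appear there without named instruments. Section 5.3 plans "Longitudinal analyses across baseline, 1/2, 3, and 6 months using" linear mixed-effects models. Among the secondary hypotheses in section 1 is "TG-iConquerFear will not affect the prevalence of physical symptoms".

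**The concern.** An SAP should settle which instrument, at which time point and by which analysis each protocol outcome will be judged. Here it changes the quality-of-life instrument, stops naming two kinds of outcome that the protocol schedules, and leaves the last follow-up out of its only longitudinal model. It gives no reason for any of these.

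Two things are at stake. An analyst who follows the SAP literally would look for quality-of-life data on an instrument that the protocol text does not list, and would leave scheduled T3 data out of the longitudinal analysis. In addition, a reader of the eventual report could not tell a planned change from an oversight, because the protocol and the SAP support different sets of outcomes and time points.

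The hypothesis of no effect on physical symptoms is a smaller, related matter. The protocol lists bodily distress as an ordinary secondary outcome. The SAP states an expected null and gives no margin or interval criterion by which that could be shown.

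**Working it through.** No figure in the plan bears on this point and no formula applies. The check sets the two documents side by side.

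| Item | Protocol | SAP |
|---|---|---|
| Global quality of life, VAS | Screening questionnaire, timeline, secondary outcome | Not named |
| Global health, VAS | Screening questionnaire, secondary outcome | Not named |
| EQ-5D-5L | Not in the screening questionnaire, timeline, secondary outcomes or economic measures | Section 4, its only mention in the documents |
| Health anxiety, Whiteley-8 | Screening questionnaire, timeline, secondary outcome | Not named |
| Bodily distress | Screening questionnaire, timeline, secondary outcome | Section 1 hypothesis of no effect; section 5.5 exploratory association; perhaps meant by distress in section 4 |
| One year (T3) | Planned for the FCRI and all secondary outcomes | Not in the section 5.3 mixed model; not mentioned in any section |

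1. **Quality of life.** Section 5.3 analyses continuous secondary outcomes by paired tests and change scores, so each needs a baseline. The protocol describes the content of the screening questionnaire (Part 1) and of the extra questions for those at or above the cut-off (Part 2). EQ-5D-5L is in neither description. The VAS items are in the first.

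2. **Health anxiety and bodily distress.** SAP sections 4 and 5.5 treat functional and psychiatric disorders as exploratory associations. That is a different question from the between-arm effect on Whiteley-8 or bodily distress, which is what the protocol's secondary outcomes ask.

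3. **One year.** The protocol's study plan (Fig. 4) gives follow-ups at ½, 3, 6 and 12 months. The SAP model uses baseline and the first three of these. One of four follow-ups is therefore left out.

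4. **General cover in the protocol.** The protocol's Statistical analysis section says that the effect on every secondary outcome will be analysed. It plans mixed models without excluding a time point, and tests of the proportion above the cut-off at every follow-up. Read with the definition of secondary outcomes, this includes the VAS items, Whiteley-8 and T3. The SAP, the more specific document, does not carry it through.

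5. **Explanation.** The deviations listed in the SAP's update of 10 January 2025 concern per-protocol, mediator, predictor and economic analyses. None concerns the quality-of-life instrument, health anxiety or T3.

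**The case against.** The best defence is that nothing has been lost. The protocol's statistical section already promises an analysis of every secondary outcome and every follow-up, and the SAP's change-score tests carry no time limit. Its unspecified anxiety scales could include health anxiety, and its distress could mean bodily distress. This stands against any statement that the VAS items, Whiteley-8 or T3 have no analysis at all. It does not remove the conflict, because the SAP names a different instrument and a shorter set of time points.

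A reader might infer four stronger things that the documents do not support:

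- **That EQ-5D-5L was never administered or has no baseline.** The questionnaires are in the protocol's appendix 6, which is not part of the text available here. What can be shown is that the protocol text does not list the instrument.
- **That the quality-of-life part of the aim cannot be answered.** Quality of life is in the Aim, but the FCRI total is the sole primary outcome and the basis of the sample size. The VAS items remain protocol secondary outcomes with general analysis cover.
- **That the SAP will take P > .05 as proof of no effect on physical symptoms.** It states an expectation and calls secondary analyses hypothesis-generating. It sets out no such rule.
- **That outcomes were dropped selectively.** The documents show an unexplained difference, not a motive.

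**Conclusion.** The point holds as an unresolved conflict between the protocol and the SAP. Three scheduled measures (global quality of life VAS, global health VAS, Whiteley-8) are not named in the SAP as treatment outcomes. One of four follow-ups is outside its mixed model, and one SAP instrument has no collection point in the protocol text. This is more than missing detail, because following the SAP literally would change what is analysed. It does not touch the primary FCRI comparison at 3 months.

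The conclusion assumes that the questionnaire appendix agrees with the protocol text. If the appendix contains EQ-5D-5L, that instrument has a data source, but the VAS items, Whiteley-8 and T3 still lack a named SAP analysis.

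**What to change.** Issue a dated SAP addendum. The January 2025 update already reports in the past tense which analyses were not done, so section 4 should not be edited silently. The addendum should:

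- restore the global quality of life VAS, the global health VAS, Whiteley-8 and bodily distress as the protocol's secondary outcomes, each with instrument, time points and analysis;
- remove EQ-5D-5L or, if it was collected, state when it was added and report it as additional to the VAS items;
- add T3 (12 months) to the mixed model in section 5.3, or record among the deviations why T3 was not analysed;
- require the physical-symptom result to be reported as a between-group difference with a 95% CI, with no claim of no effect from a non-significant test.

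The cost is wording and a few additional model runs on data that the protocol already schedules. Where those data are not available, a sentence among the deviations saying so is enough.

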### Exploratory outcomes

- Dropout patterns (demographic and psychosocial predictors of attrition).
- Process measures (eg, illness uncertainty, perceived risk of recurrence, negative beliefs about worry) as potential mediators.
- Associations with functional somatic and psychiatric disorders (using validated cut-offs).

## 5. Statistical methods

### 5.1 Descriptive statistics

- Baseline demographics and cancer-related characteristics summarized as means (SD), medians (IQR), or proportions.
- Between-group balance assessed using standardized differences ( $>0.20$  = imbalance).

### 5.2 Primary analysis

- Within-group changes from baseline to follow-up assessed with paired *t*-tests.
- Between-group differences in mean change scores tested using 2-sample *t*-tests (or non-parametric equivalent if assumptions violated).
- Effect size (Cohen's *d*) and 95% CI reported for between-group differences at 3 months.

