### Part 2, recruitment

In cases where participants in Part 1 report a FCRI-SF score  $\geq 22$  indicating likely clinically significant FCR [44], they will automatically be asked if they want to hear more about an experimental intervention targeting FCR, and 12 more questions appears on uncertainty in illness, negative beliefs about worry and perceived risk of cancer recurrence along with the full version of the FCRI (appendix 6). See Fig. 2 for timeline[45].

All survivors with likely clinically significant FCR who agree to be contacted by a research assistant (primary investigator or one of the two psychologists who will perform the intervention. All has been sufficient trained) will be telephoned, informed orally about the RCT and interviewed using the mini-SCAN, a brief semi-structured interview for psychiatric diagnosis [46]. This interview is designed to ensure appropriate treatment is offered to prospective study participants. If information and miniSCAN cannot be performed at the same time, a new appointment will be made. In case of severe depression or severe psychiatric or cognitive disorder, the survivor will be excluded from the study and encouraged to seek relevant help through their general practitioner. When needed, the research assistant can consult a psychiatrist. Supervision will be performed on regular basis.

The contacting research assistant will declare oral information given (appendix 4. Erklæring om videregivelse af mundtlig information) and for potential participants meeting eligibility criteria initiate for RedCap to send out written participant information sheet (appendix 3.

Deltagerinformation) and consent form (appendix 5. Samtykkeerklæring til projektdeltagelse) to the participant's E-boks. By entering their Nem-id (a Danish secure personal coding system for electronic movements) they will consent to participation and concealed, computerized variable block randomization (1:1) stratified for age and gender will happen immediately.

Fig. 2, Timeline

|                          | STUDY PERIOD         |           |               |              |                 |           |
|--------------------------|----------------------|-----------|---------------|--------------|-----------------|-----------|
|                          | Population Screening | Enrolment | Randomization | Intervention | Follow-up       | Close-out |

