## EVALUATION

### Primary outcome measure

The primary outcome measure is the 3 month follow-up (T1) total score on the recently validated Danish version of the FCRI [13]. The FCRI is a 42-item self-report measure that includes subscales assessing FCR triggers, severity, psychological distress, functioning impairments, insight, reassurance, and coping strategies [48]. The FCRI has demonstrated high: internal consistency ( $\alpha=0.96$ ) [49], interclass correlation (0.84) [13] and convergent validity in large heterogeneous cancer survivor samples. Respondents rate the degree to which symptoms/issues affected them over the past month on a Likert scale ranging from 0 ('not at all' or 'never') to 4 ('a great deal' or 'all the time'). While there are potential issues with aggregating FCRI subscales [50], total FCRI score will be used as the dependent variable, as it closely reflects proposed features of clinically significant FCR; namely related distress, functional impact, and maladaptive coping[2], rather than the level of fear indicated by the FCRI-SF [50, 51]. Total scores can range from 0-168; higher scores indicate greater FCR morbidity. Level of FCR will be measured post-treatment (T0) and at follow-up after 3 (T1) and 6 (T2) months. Long-term effect will be evaluated after one year (T3). All electronic questionnaires will be sent out automatically through RedCAP.

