### Statistical analysis

A flowchart of participants and dropouts following the CONSORT guidelines will be drawn.

STATA will be used for all statistical analyses. All statistical tests will be two-sided (level of significance = 0.05).  $\chi^2$ -tests will be performed on all follow-up data to analyse proportions of participants above or below the clinical cut-off.

The influence of the intervention will be analysed for the primary outcome and for all secondary outcomes. Linear mixed effects models will be used to analyse longitudinal differences between intervention and control group. Association with functional disorders (health anxiety and bodily distress symptom) and psychiatric disorders (anxiety and depression) will be evaluated with adjusted and unadjusted linear regressions analyses on baseline data.

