## 4. Outcomes

### Primary outcome

- Change in FCRI total score from baseline to 3 months.

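### The primary analysis tests FCRI change without baseline FCRI, age or gender as covariates: the randomised comparison stays valid, but its interval is likely to be wider than the collected data allow

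*Combined protocol and SAP*

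**What the plan says.** SAP section 4 defines the primary outcome as "Change in FCRI total score from baseline to 3 months". SAP section 5.2 then lists two tests under the primary analysis. The first is "Within-group changes from baseline to follow-up assessed with paired" t-tests. The second is "Between-group differences in mean change scores tested using 2-sample" t-tests, with a non-parametric alternative if assumptions fail. No covariate is named, and no criterion is given for moving to the alternative.

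The protocol (Primary outcome measure) words the endpoint differently: "The primary outcome measure is the 3 month follow-up (T1) total score". Its Statistical analysis section covers primary and secondary outcomes and says that "Linear mixed effects models will be used to analyse longitudinal differences between intervention and control group", again without covariates. In the SAP, the mixed model appears only in section 5.3, as a secondary analysis with group, time, their interaction and a random intercept.

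The protocol (Part 2, recruitment) describes "computerized variable block randomization (1:1) stratified for age and gender will happen immediately". The same section has the full FCRI completed before randomisation by those who reach the FCRI-SF cut-off of 22. Age and sex come from the registry (Register data, Baseline data).

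**The concern.** The three variables most obviously suited to adjustment are already in the database, and no analysis of the treatment effect in either document uses them as covariates. The protocol's adjusted regressions concern associations at baseline. Its promise to take dropout differences into account names no variable or model.

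A change score assumes that each point of baseline FCRI carries forward as one point at follow-up. Entry required a high FCRI-SF score, and the full FCRI was collected as part of the same screening process. Some regression to the mean is therefore expected, and the true slope is probably below 1. The change score then over-corrects chance baseline differences and carries avoidable noise.

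Precision is scarce in this trial. The September 2023 update reduced the target to 68 participants, and the January 2025 list of deviations drops the mediator, predictor and economic analyses at least partly for lack of power.

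The paired t-tests raise a related problem of presentation. In a sample selected for high scores, both arms may improve without any treatment effect, and a within-group P value listed under the primary analysis invites misreading.

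**Working it through.** **The plan's own figure.** The protocol's inputs are a difference of 3.5, SD 7, 90% power and two-sided alpha 0.05. An exact t calculation gives 86 per arm, or 172 analysed, not 246. Since 172/0.7 = 246 and 246/0.7 = 351, the 30% dropout allowance seems to have been applied twice. That is a separate matter. The SE ratio below does not depend on N or on the SD.

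**Inputs.**
- Analysed per arm: 68 × 0.8 = 54.4, so about 27 (SAP, September 2023 update).
- Illustrative effect: 3.5/7, d = 0.5 (protocol, Power calculation). The protocol does not say whether the SD is of scores or of changes; it is taken here as the score SD.
- Correlation ρ between baseline and follow-up: not given. Assumed range 0.3 to 0.84. The upper end borrows the reliability coefficient quoted in Primary outcome measure, which is not a baseline-to-follow-up correlation in this trial.
- SDs at the two times: assumed equal.

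**Formulas.** In units of the score variance:
- change score: v = 2(1 − ρ)
- ANCOVA: v = 1 − ρ²
- SE ratio, ANCOVA to change score: √[(1 − ρ²)/(2(1 − ρ))] = √[(1 + ρ)/2]
- 95% half-width: t × 7 × √(v × 2/27), with 52 df for the change score and 51 for ANCOVA
- power: noncentral t with noncentrality (0.5/√v) × √(27/2)

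| ρ | v, change | v, ANCOVA | SE ratio | Change-score CI wider by | Half-width, change → ANCOVA | Power at d = 0.5 |
|---|---|---|---|---|---|---|
| 0.3 | 1.40 | 0.91 | 0.806 | 24% | 4.52 → 3.65 | 33% → 47% |
| 0.5 | 1.00 | 0.75 | 0.866 | 15% | 3.82 → 3.31 | 44% → 55% |
| 0.7 | 0.60 | 0.51 | 0.922 | 8% | 2.96 → 2.73 | 64% → 71% |
| 0.84 | 0.32 | 0.294 | 0.959 | 4% | 2.16 → 2.08 | 89% → 91% |

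Estimating the slope from 54 people multiplies the ANCOVA SE by about √(1 + 1/50) = 1.01. The half-widths become 3.68, 3.35, 2.76 and 2.10, and power falls by less than one point. Below ρ = 0.5, v for the change score exceeds 1, so it is less precise than comparing follow-up scores alone.

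**Equal-SD assumption.** If the follow-up SD is k times the baseline SD, the change-score variance exceeds the ANCOVA variance by (1 − ρk)² times the baseline variance. The excess is never negative and vanishes when ρk = 1.

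**Larger effect.** With 27 per arm, 95% power implies d of about 1.0. At d = 1.0 on the score SD, power goes from 86% to 97% (ρ = 0.3) and from 95% to 99% (ρ = 0.5), and exceeds 99% either way at 0.7 and above.

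**Strata.** Two binary factors were added to the baseline ANCOVA in a simulation with 27 per arm and 4,000 runs per setting. At ρ = 0.5 the half-width went from 3.32 to 3.39 if the factors were not prognostic, from 3.33 to 3.32 if they explained 5% of residual variance, and from 3.33 to 3.23 at 10%. The change score gave 3.80 to 3.81. The narrowest margin in any setting was 2.13 against 2.16 (ρ = 0.84, factors not prognostic). The simulated allocation was not stratified, so the 2% cost is probably on the high side.

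**The mixed model.** With complete data and unconstrained baseline means, the group-by-time contrast in section 5.3 equals the difference in mean change. It does not recover the loss.

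**The case against.** The strongest reply is that the planned test is legitimate and the loss may be small. This largely stands.

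- A change score does use baseline, by subtraction. A reader might infer that baseline is ignored; what is missing is adjustment with an estimated slope.
- A reader might infer bias from regression to the mean. It acts on both randomised arms alike, so the between-group test remains valid. The SAP's primary hypothesis is between-group, and nowhere does the plan attribute within-group change to treatment. Placing the paired tests under the primary analysis is a weakness of labelling. The documents give no population mean FCRI total, so the expected drift cannot be put in points.
- A reader might infer that omitting age and gender inflates the standard error. The documents do not say that either predicts FCRI, and if neither does, adding them gains nothing.
- The power illustration joins d = 0.5 from the 350-participant plan to the sample size of the 68-participant plan, which was revised for a larger effect. It describes neither plan, and at the larger effect the gain is smaller.
- The rank-test alternative is pre-specified. The fair criticism is that its trigger is not, so the choice is left until the data are seen, and a rank test does not estimate a mean difference.
- The January 2025 update reports omitted analyses in the past tense and says that five passive users gave no outcome data. Replacing the primary test now may itself be a change made after seeing data. This changes the remedy, not the point.

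**Conclusion.** The point holds as a matter of precision. Section 5.2 does not adjust for baseline FCRI, age or gender, and nothing elsewhere in the plan makes up for it. Under equal SDs the change-score interval is about 4% to 24% wider than under ANCOVA for ρ from 0.84 to 0.3. Equivalently, ANCOVA needs (1 + ρ)/2 of the change-score sample, 92% down to 65%. Selection on FCRI-SF may lower ρ, which would enlarge the loss, but no document figure shows where ρ lies. The direction is secure with equal SDs; the size is not. Nearly all of the gain comes from baseline. The documents do not support a claim of a biased treatment effect or an invalid test.

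**What to change.** - **Primary analysis.** Specify an ANCOVA of FCRI total at the primary time point on arm, baseline FCRI total, age and gender, with age entered in a stated form. A mixed model with baseline means constrained equal and the same terms would also serve. Report the adjusted difference with its 95% CI.
- **Assumptions.** Replace the open-ended switch to a rank test with robust or bootstrap standard errors, so that the estimand stays a mean difference.
- **Paired t-tests.** Move them out of section 5.2 and label them descriptive, noting that both arms were selected for high scores.
- **Time point.** Reconcile the endpoint before fixing the model. The protocol's Primary outcome measure uses the T1 score at 3-month follow-up, after a separate post-treatment assessment. SAP section 1 says 3 months after the intervention. SAP section 4 counts from baseline to 3 months. The protocol's Process of participation puts the first follow-up 12 weeks after consent and the second 12 weeks later.
- **Timing of the change.** If outcome data have already been examined, keep the specified t-test and report the ANCOVA beside it, labelled as added later.

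No new data are needed. Before any look at outcomes the cost is SAP wording and the decision on the time point; after it, the further cost is that the adjusted result cannot be presented as pre-specified.
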